#### Sample size {14}

Randomized controlled trials conducted with participants with burn wounds are scarce, hindering the calculation of the effect size. Thus, a conservative effect size (0.5), 80% power, and 95% probability (*α* = 0.05) were used for the primary outcome (re-epithelialization rate), generating a sample size of 30 participants (three groups of ten participants). The sample size for repeated measures ANOVA was calculated using the G* Power 3.1.0 software (Christian-Albrechts-Universitat, Kiel, Germany). Considering a possible sample loss of 30%, we intend to recruit 39 participants.

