### Study objectives

#### Primary objective

The primary objective is to determine whether LED photobiomodulation is superior to simulation to increase the re-epithelialization rate and decrease the healing time of burn wounds.

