**Fig. 2 Fig2:**
[figure not shown]
Participant timeline

Sociodemographic data, characteristics of the burn (i.e., type of accident, causal agent, and percentage of body surface affected), when the burn happened, and pharmacological treatment received will be registered on an evaluation form. Participants will be instructed to maintain standard care. A trained researcher will assess and perform therapeutic procedures five times a week, once daily. Wound healing rate, pain, pruritus, skin temperature, mobility restriction, and scar quality will be analyzed.

Digital images of the burned area, skin temperature (infrared image), and pain and pruritus will be assessed daily before therapeutic procedures. Only three assessments will be analyzed: initial (before treatment), final (when re-epithelialization of the burn is complete), and one assessment between initial and final assessments (median time of treatment between initial and final assessment). After treatment and total wound closure, mobility and scar quality will be assessed using the adheremeter and Vancouver Scale, respectively.

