### Assignment of interventions: allocation

#### Sequence generation {16a}

The online software randomization.com will be used to allocate participants by blocks into three parallel groups (1:1:1) of 13 subjects: RLG, which will receive photobiomodulation using red LED; ILG, which will receive photobiomodulation using infrared LED; and SG, which will undergo a simulated application of LED therapy.

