## Statistical methods

### Statistical methods for primary and secondary outcomes {20a}

Outcome variables will be re-epithelialization rate, presence and intensity of pain and pruritus, local skin temperature, and scar mobility and quality. Groups will be considered independent variables. Statistical analysis will be performed according to intention-to-treat principles. Descriptive analyses and histogram inspections will determine data normality. Between-group differences and 95% confidence intervals (95% CI) will be calculated using linear mixed models and group, time, and group-versus-time interaction terms. A first-order autoregressive covariance matrix will be considered. Group and time will be considered fixed factors, and participants the random factors. A Q-Q plot will be performed for all variables to consistently and similarly confirm the normality of residues between groups. The SPSS software version 20.0 (IBM SPSS Corp., Armonk, NY) will be used for data analysis.

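### The sample size calls an unlabelled effect size of 0.5 conservative: read as Cohen's f it is a gap above one SD, and the 80% power is not shown for the LED-sham contrasts

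*Protocol article*

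**What the plan says.** Under Sample size {14}, the protocol article explains that burn trials are too scarce for an effect size to be calculated. It continues: "Thus, a conservative effect size (0.5), 80% power, and 95% probability". The primary outcome is the re-epithelialization rate and the result is three groups of ten, raised to 39 for a possible 30% loss. On method it says only that "The sample size for repeated measures ANOVA was calculated using the G* Power 3.1.0 software". It does not say whether 0.5 is Cohen's f or a standardized mean difference. Nor does it say whether the group, time or group-by-time effect was tested, or how many measurements and what correlation were entered.

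The Primary objective is to "determine whether LED photobiomodulation is superior to simulation". The analysis section {20a} says "Between-group differences and 95% confidence intervals (95% CI) will be calculated using linear mixed models", with group, time and group-by-time terms. Under the participant timeline {13}, "Only three assessments will be analyzed: initial (before treatment), final (when re-epithelialization of the burn is complete), and one assessment between initial and final assessments".

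**The concern.** A conservative effect size should be small enough that plausible smaller benefits are unlikely to be missed. A reader who sees 0.5 with that label will probably think of half an SD between LED and sham. On the scale the named software uses, 0.5 is a much larger difference. The 80% is also not tied to the comparison the trial is meant to answer, which is each LED arm against sham.

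At stake is how a null or imprecise result is read. With a conservative effect and 80% power on record, it could be taken as evidence that LED has no worthwhile benefit, when the trial could reliably find only a very large one.

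**Working it through.** **Inputs from the article.** Effect size 0.5, power 0.80, alpha 0.05, three equal groups, 30 in total (10 per arm), 39 recruited (13 per arm), three analysed assessments. **Assumption:** correlation rho = 0.5 between assessments, which the article does not give.

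**1. Reproducing 30.** For the between-group test, lambda = f² × N × m / (1 + (m − 1) × rho), with 2 and N − 3 degrees of freedom. With f = 0.5, m = 3, rho = 0.5 and N = 30, lambda = 0.25 × 30 × 3 / 2 = 11.25 and power is 0.817. N = 27 gives 0.766, so 30 is the smallest balanced total. The match depends on rho: 0.3 gives 24, 0.6 gives 33 and 0.7 gives 36.

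**2. Other settings that give 30** (three groups, alpha 0.05):

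| Tested effect | Setting | Power at N = 30 |
|---|---|---|
| Group-by-time | f = 0.5 on the partial-eta-squared scale, m = 3 | 0.816 |
| Group-by-time | f = 0.25, m = 3, rho = 0.6 | 0.833 |
| Group-by-time | f = 0.25, m = 4, rho = 0.5 | 0.809 |
| Time | f = 0.25, m = 3, rho = 0.5 | 0.840 |

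The total of 30 therefore does not identify the test.

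**3. What f = 0.5 means for the group effect.**
- Both LED arms equal, sham apart: d = 3f/√2 = 1.5/1.414 = 1.06 SD.
- Three arms evenly spread: extreme arms differ by f√6 = 0.5 × 2.449 = 1.22 SD, and the middle arm lies 0.61 SD from sham.

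**4. Power of one LED-sham contrast.** Two-sided t test, alpha 0.05, no multiplicity adjustment. Averaging three assessments at rho = 0.5 multiplies the SD by √((1 + 2 × 0.5)/3) = 0.816.

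| True LED-sham gap | 10 per arm, single | 10 per arm, averaged | 13 per arm, single | 13 per arm, averaged |
|---|---|---|---|---|
| 0.5 SD | 18.5% | 25% | 23% | 32% |
| 1.06 SD | 61% | 78% | 74% | 89% |
| 1.22 SD | 74% | 89% | 85% | 96% |

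The columns for 13 per arm apply only if nobody is lost.

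**5. Which columns apply.** Percent healed is zero by definition before treatment and complete by definition at the final assessment, so only the middle assessment can separate the arms. Days to healing, the other part of the primary outcome, is one value per participant. In both cases the single-assessment columns are the relevant ones. With one informative assessment, even the three-group test at f = 0.5 has power 0.635 at N = 30 (one-way ANOVA, lambda = 0.25 × 30 = 7.5).

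**The case against.** The strongest reply is that the article never says which effect was powered. A reader might infer from the match in step 1 that the 80% belongs to an overall group effect averaged over visits. The documents do not support that as fact: the match needs a correlation of about 0.5 that is not stated, and step 2 shows group-by-time and time settings that fit as well. If the interaction was powered, it is a term in the planned model. This stands, and the point must be made conditionally.

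It does not rescue the label. On the usual scale, an interaction f of 0.25 still corresponds to an LED-sham gap of about 1.1 SD if the two LED arms are equal and only the middle assessment differs, or about 1.3 SD at the last assessment if the gap grows linearly. The time-effect reading does not power LED against sham at all.

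A reader might also infer that the 80% fails for every LED-sham comparison. That is too strong. At 1.06 SD, the averaged contrast has 78% power with 10 per arm, close to nominal, and 89% with 13. If the objective means both LED arms together against sham, the figures with 10 per arm are 90% averaged and 75% at one assessment. The averaged figures, however, draw on two assessments at which percent healed cannot differ.

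Two further replies are fair. Software settings may sit in the full protocol, so their absence from an article is not in itself the fault. And the planned 95% confidence intervals will show the imprecision. Neither makes the published pairing of a conservative effect with 80% power correct.

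**Conclusion.** The point holds in conditional form. The article admits it has no data behind 0.5, does not say what 0.5 measures, and still calls it conservative. Neither natural reading sustains both the label and the 80%. As f for the group effect, 0.5 is a gap of 1.06 to 1.22 SD, which is large. As half an SD between LED and sham, power for one contrast is 18.5% to 25% with 10 per arm and 23% to 32% with 13. For the contrasts the objective and analysis sections target, 80% is not shown: a 1.06 SD contrast has 61% power at the informative assessment with 10 per arm, and 74% with 13.

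The averaged figures assume a correlation of 0.5, and all contrast figures are unadjusted for two comparisons. No conversion to days or percent healed is offered, because the article gives no SD for either. This is a fault in the stated justification and should be corrected; it does not invalidate the design.

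**What to change.** Keep 39 participants. In Sample size {14}:

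- delete the word conservative;
- state the metric, tested effect, number of measurements and correlation actually entered, taken from the sponsor's own record and not from the reconstruction above;
- translate 0.5 into an LED-sham difference in SD units (about 1.1 to 1.2 SD if it is f for the group effect);
- give the power of each LED-sham contrast at the informative assessment;
- state that smaller effects cannot be excluded by this trial.

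The cost is a few sentences and less favourable stated figures. No participants, visits or procedures change.

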#### Primary outcome measures

##### Re-epithelialization rate

The percentage of healed skin tissue (re-epithelialization rate) and the number of days between the start of treatment and total healing process will be assessed using digital images of the burned region. These images will be captured daily from before treatment to follow-up of the re-epithelialization process. A digital camera (Sony Cyber-Shot Dsc-W800, 20.1 megapixels, Brazil) will be positioned on a tripod, parallel to the ground and perpendicularly fixed at a distance of 30 cm from the area to be treated. If the participant cannot stand, images will be captured on a stretcher assuring the same distance and a 90° angle between the area and the camera. The photograph will be captured on a white background with indirect artificial lighting.

Re-epithelialization rate will be assessed by counting the days until complete healing and monitoring the wound area during protocols (ImageJ® software, version 1.36 b). The crust area on the wound edge will be measured using digital image analysis, according to Gabison et al. [19]. The software converts the selected area to cm^2^ by associating the known dimension of the photographed object, area of interest, and the respective number of pixels. Healing will be assessed using a glossary of healing evolution based on the pressure ulcer assessment scale proposed by Bates-Jensen, Vredevoe, and Brecht [20].

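### The 80% power comes from a repeated-measures calculation that does not fit days to healing, which gives one value per participant; at f = 0.5 the power is about 64% with 30 evaluable

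*Protocol article*

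**What the plan says.** The section Sample size {14} sizes the trial for the re-epithelialization rate. Its inputs are an effect size of 0.5 with no metric named, and "80% power, and 95% probability", which the text equates with alpha = 0.05. The result is given as "generating a sample size of 30 participants (three groups of ten participants"), and the method in the words "The sample size for repeated measures ANOVA was calculated using the G* Power 3.1.0 software". Then: "Considering a possible sample loss of 30%, we intend to recruit 39 participants".

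The outcome is defined elsewhere. Under Re-epithelialization rate (Outcomes {12}) the primary outcome has two parts, the percentage of healed tissue and the number of days to total healing. The section continues: "Re-epithelialization rate will be assessed by counting the days until complete healing", together with monitoring of the wound area in cm². The Primary objective names both aims, to "increase the re-epithelialization rate and decrease the healing time of burn wounds".

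The text under Participant timeline {13} limits which of the daily images are used: "Only three assessments will be analyzed: initial (before treatment), final (when re-epithelialization of the burn is complete), and one assessment between initial and final assessments". The one in between is placed at the middle of each participant's own treatment period. Intervention description {11a} continues treatment until the wound has closed.

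**The concern.** A repeated-measures ANOVA gains power over a single-value comparison only if each participant contributes more than one measurement that carries information on treatment. The primary outcome, as the protocol defines it, hardly does.

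- **Days to healing** is one number per participant.
- **Percent healed** is analysed at three times. It is 0% before treatment, and it is 100% at the last assessment because that assessment is defined by closure. Only the middle value can vary among those who heal.

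If the sample size rests on information that the outcome does not contain, the stated 80% power is too high at the plan's own effect size and alpha. The chance of missing the assumed effect on days to healing would be over one in three instead of one in five. Readers who rely on the stated power to interpret a null result would be misled to that extent.

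**Working it through.** **Inputs.** From Sample size {14}: effect size 0.5, alpha 0.05, power 80%, k = 3 groups, N = 30, 39 recruited. From Participant timeline {13}: m = 3 analysed assessments. Assumed, because the article does not state them: 0.5 is Cohen's f (the metric of the ANOVA routines), and where a correlation is needed rho = 0.5 (the software default). All powers are from the noncentral F distribution with noncentrality lambda.

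**Step 1: reproduce N = 30.** Two routines do so.

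(a) Between-factors test: lambda = N f² m / (1 + (m − 1) rho), df = 2 and N − 3.
- N = 30: lambda = 30 × 0.25 × 3 / 2 = 11.25, df 2 and 27, power 81.7%.
- N = 27: lambda = 10.125, power 76.6%.
- The smallest balanced N is 30, as stated.

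(b) Within-between interaction, alternative effect-size option: lambda = f² (N − 3)(m − 1), df = 4 and 2(N − 3).
- N = 30: lambda = 0.25 × 27 × 2 = 13.5, df 4 and 54, power 81.6%.
- N = 27: lambda = 12.0, power 75.7%.
- The smallest balanced N is again 30.

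Under the default option the interaction test with m = 3 and rho = 0.5 would need only 12, so the option matters. Other between-factors inputs also return 30 (m = 4 with rho = 0.5; m = 2 with rho = 0.3). Every one of these sets uses more than one measurement per participant.

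**Step 2: one value per participant.** This is a one-way comparison of three groups: lambda = N f², df = 2 and N − 3. It needs neither m nor rho.

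| N analysed | lambda = 0.25 N | Power |
|---|---|---|
| 30 | 7.50 | 63.5% |
| 39 (no loss) | 9.75 | 76.9% |
| 42 | 10.50 | 80.3% |

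The smallest balanced N for 80% is 42. At N = 30 the chance of a miss is 100 − 63.5 = 36.5%.

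**Step 3: detectable effect.** Solving for f at 80% power gives 0.60 at N = 30 and 0.52 at N = 39.

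**Step 4: wound area in cm².** Here the first value differs between participants, although it precedes treatment, and the last is zero. If the middle value is adjusted for the first with correlation r, lambda = N f² / (1 − r²), df = 2 and N − 4. At N = 30:

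| Assumed r | lambda | Power |
|---|---|---|
| 0.5 | 7.5 / 0.75 = 10.0 | 76.5% |
| 0.6 | 7.5 / 0.64 = 11.7 | 83.2% |
| 0.7 | 7.5 / 0.51 = 14.7 | 90.9% |

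The article gives no such correlation.

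**The case against.** The strongest reply is that the source of the 30 is not known. The article names only a repeated-measures ANOVA. A reader might infer that the software credited each participant with 3/2 = 1.5 times the information of a single value, and that removing this factor turns 80% into 64%. That describes routine (a) only. Routine (b) fits equally well, suits the group-by-time term planned under Statistical methods {20a}, and contains no such factor. Its 0.5 is an interaction effect size, which does not translate directly into 0.5 for a one-way comparison. This stands: the 64% is the power of a one-way test at f = 0.5, not a conversion of a known calculation.

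A second reply is that wound area is also monitored and that a mixed model can use its starting value. This stands too. As Step 4 shows, power for area may lie on either side of 80%. The statement under {20b} that no adjusted analyses are planned does not settle it, since a baseline can enter the model as one of the repeated outcomes.

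Third, the middle assessment falls at each participant's own mid-treatment point, so faster healers are measured earlier. Whether percent healed at that point could show an effect of f = 0.5 is doubtful, and 64% should not be offered as its power. This is why the restatement should be tied to days to healing.

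Finally, the article openly says that trials are scarce and that 0.5 is conventional, and a detectable f of 0.52 to 0.60 is not far from 0.50. That limits the weight of the point. It does not make the stated 80% right for a single-value outcome.

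**Conclusion.** The point holds in a limited form. The repeated-measures calculation, whose inputs are unstated, does not match days to healing, nor percent healed when only one of its three analysed values can vary among those who heal. For one value per participant at f = 0.5 and two-degree-of-freedom alpha 0.05, power is about 64% at 30 evaluable and 77% at 39 with no loss. The nine extra participants are the allowance for loss, and even if none is lost they do not restore 80%.

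This rests on reading 0.5 as Cohen's f and accepting it, the overall three-group test and alpha as stated. If 0.5 were Cohen's d (f about 0.25), one-way power at 30 would be about 20%, so the reading used is the favourable one.

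A reader might go further and conclude that the 80% fails for every part of the primary outcome, or that 30 is an arithmetic error. The document supports neither. The 30 reproduces, and for wound area in cm² the 80% is unverified, not refuted. The fault is a mismatch between the sizing model and the outcome.

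**What to change.** Rewrite Sample size {14} for days to healing as a three-group comparison of one value per participant. Name 0.5 as Cohen's f, if that is what was meant. Then report either the power (about 64% at 30 evaluable, 77% at 39 with no loss) or the effect detectable with 80% power (f about 0.60 at 30, 0.52 at 39). Keep the repeated-measures calculation only for outcomes with informative repeated values, namely pain, pruritus and skin temperature, and state its routine, effect-size option, number of measurements and correlation. If a power is to be claimed for wound area, state the assumed baseline correlation.

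The cost is one rewritten paragraph and a less favourable stated power. Recruitment and procedures do not change, and no added enrolment is asked for.

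### Recruiting 39 covers a loss of about 23%, not the stated 30%; a full 30% loss would leave about 27 of the 30 participants calculated

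*Protocol article*

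**What the plan says.** Under Sample size {14}, the protocol article takes "a conservative effect size (0.5") with "80% power, and 95% probability" (α = 0.05), and says that these values "were used for the primary outcome (re-epithelialization rate"), "generating a sample size of 30 participants (three groups of ten participants"). It names the method: "The sample size for repeated measures ANOVA was calculated using the G* Power 3.1.0 software". The allowance for loss follows: "Considering a possible sample loss of 30%, we intend to recruit 39 participants".

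The same target appears under Sequence generation {16a}, where participants are allocated "into three parallel groups (1:1:1) of 13 subjects". The Abstract also has three groups of 13, and the Discussion has 39 participants. No section gives another loss rate or a larger target.

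**The concern.** The required number, the expected loss and the recruitment target are all stated, and they do not fit together. A loss allowance is meant to ensure that the required number is still there after the loss. Here the loss was added as a percentage of the required number, although it will be taken from the larger number recruited. If the planned loss occurs in full, the trial ends with fewer participants than its own calculation asks for.

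At stake is the accuracy of the only stated basis for the trial's power. A reader would conclude that 80% power is protected against a 30% loss, and it is not. With only ten required per group, one fewer in each group is a tenth of the required sample.

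**Working it through.** **Inputs from the protocol article**
- Required number: 30, ten in each of three groups (Sample size {14}).
- Loss: 30%. Recruitment: 39 (Sample size {14}).
- Effect size 0.5, power 80%, α = 0.05, repeated measures ANOVA in G*Power (Sample size {14}).
- Three assessments analysed: "Only three assessments will be analyzed" (Participant timeline {13}, text under Fig. 2). The sample size section does not say that three was the number entered.

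**Inputs assumed, because the article does not give them**
- 0.5 is Cohen's f.
- The correlation between repeated measurements is 0.5.
- The test is the between-groups effect.

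**Step 1. Reproduce the stated 39.**
- Multiplying up: 30 × (1 + 0.30) = 39. This matches.
- Dividing by the retained fraction: 30 / (1 − 0.30) = 42.9, so 43. This does not match.

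The target therefore comes from multiplying by 1.30.

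**Step 2. What 39 delivers.**
- Remaining after 30% loss: 39 × 0.70 = 27.3, about 27, or nine per group.
- Largest loss that still leaves 30: (39 − 30) / 39 = 9/39 = 23.1%.

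Steps 1 and 2 use only figures in the article.

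**Step 3. What a 30% loss needs.**
- 30 / 0.70 = 42.9, so 43; 43 × 0.70 = 30.1.
- For equal arms, the next multiple of three is 45 (15 per group); 45 × 0.70 = 31.5.

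**Step 4. Power, under the assumed inputs.** For the between-groups test with k groups, m measurements, correlation ρ and total number N, the noncentrality is λ = f² × N × m / (1 + (m − 1)ρ), with k − 1 and N − k degrees of freedom. With f = 0.5, k = 3, m = 3 and ρ = 0.5, this is λ = 0.25 × N × 3 / 2 = 0.375 N.

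| N | λ | Degrees of freedom | Power |
|---|---|---|---|
| 39 (no loss) | 14.625 | 2, 36 | 91.7% |
| 30 | 11.25 | 2, 27 | 81.7% |
| 28 | 10.5 | 2, 25 | 78.5% |
| 27 | 10.125 | 2, 24 | 76.6% |

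Under these settings 30 is the smallest balanced number with at least 80% power, so the stated 30 is reproduced. At 27, power is 80 − 76.6 = 3.4 points below the stated level.

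**Step 5. Other settings that also give 30 as the smallest balanced number.**

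| Test | f | m | ρ | Power at 27 |
|---|---|---|---|---|
| Between groups | 0.5 | 2 | 0.3 | 77.8% |
| Between groups | 0.5 | 4 | 0.5 | 79.4% |
| Within participants | 0.25 | 3 | 0.5 | 79.4% |
| Group by time | 0.25 | 4 | 0.5 | 75.4% |

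The last two rows use f = 0.25, which is not the stated 0.5; they show how far the result depends on the setting. Power at 27 is below 80% in every row. That must be so: if 30 is the smallest balanced number that reaches 80%, then 27, the next balanced number down, does not reach it.

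**The case against.** **The loss is only a possibility.** This stands in part. A reader might infer that the trial is underpowered as planned, and the article does not support that. With all 39 analysed, power is about 92% under the main settings, and the calculated 30 is still met up to a loss of about 23%. The shortfall arises only if the loss comes close to 30%. That rate is nevertheless the article's own planning figure and the only reason it gives for 39.

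**The mixed model uses partial data.** Sections {20a} and {20c} plan an intention-to-treat analysis with a linear mixed model, which can use a dropout's earlier assessments. Section {11c} also counts some missed sessions as attrition, so some participants classed as lost may still have outcome data. This may soften the loss, and 27 is then a pessimistic count. It does not rescue the sentence. The sample size section itself treats lost participants as not counting toward the 30. A participant lost before wound closure also has no final assessment and no observed time to healing.

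**Quoting 81.7% against 76.6% exaggerates the effect.** This stands. Part of the 81.7% is a surplus from rounding up to balanced groups. Against the stated 80%, the gap is 3.4 points under the main settings and less than one point under the most favourable ones.

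**Multiplying by 1.30 is common practice.** It would be right only if 30% meant 30% of those who complete. The article speaks of loss from the sample.

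**Conclusion.** The statement is wrong as written, and its severity is modest. The count needs no assumption: 39 allows for a loss of about 23%, and a 30% loss leaves about three participants fewer than calculated.

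That power falls below 80% at that loss requires only that 30 was the smallest balanced number reaching it. The size of the fall depends on inputs the article does not give, so about 77% is one value in a range of roughly 75% to 79%. A reader might take 77% as the trial's power at full loss, but the article does not support so exact a figure.

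**What to change.** Keep 39 and replace the sentence on loss with, for example: *Recruiting 39 allows for a loss of up to about 23%; with a 30% loss about 27 participants would remain, below the 30 calculated, and power would be somewhat below 80%.* Any exact power figure should come from the investigators' own G*Power inputs, with the effect-size metric, correlation, number of measurements and test named. This costs one sentence and a slightly less favourable statement. It needs no extra participants and no change to the randomisation.

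If the sponsor prefers to keep the 30% allowance, the matching target is 43, or 45 for equal arms. That means four or six more participants than now planned. For 45, the 13 per group under Sequence generation {16a} and in the Abstract would become 15, and the 39 in the Discussion would become 45.
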